#### **4. Sample size and study period**

##### **4.1. Sample size**

Total of 60 participants.

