##### **4.2. Basis for setting**

The sample size for reliability verification was calculated based on prior research, assuming ICC = 0.8, minimum acceptable ICC = 0.6,  $\alpha = 0.05$ , power  $(1 - \beta) = 0.8$ , two raters, and two measurements per participant . This calculation indicated a required sample size of 28–30 participants. For criterion-related validity, G\*Power 3.1 was used with an expected correlation coefficient  $r = 0.75$ ,  $\alpha = 0.05$ , and power = 0.95, yielding a minimum target sample size of 16 participants. Considering potential 10% data loss, 30 participants per group were planned.

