##### **5.2. Exclusion Criteria**

- (1) impaired consciousness
- (2) Cognitive impairment (Mini-Mental State Examination score of 25 or below) or a diagnosis of post-stroke cognitive impairment affecting the ability to understand instructions or perform tasks
- (3) Recurrent stroke
- (4) Visual field impairment
- (5) Bilateral upper limb motor paralysis
- (6) CNS or orthopedic disease other than stroke
- (7) Upper limb or finger joint pain during movement
- (8) Significant limitation of joint range of motion of the upper limb
- (9) Amputation of upper limb, hand, or fingers
- (10) Loss of data

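### Section 4.2 says 30 per group allows for 10% data loss, but in the reliability group 30 less 10% is 27, just below the plan's own required 28–30

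*Protocol*

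**What the plan says.** Protocol section 4.2 sets out its reasoning in three steps.

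1. Reliability: the inputs are "assuming ICC = 0.8, minimum acceptable ICC = 0.6", alpha 0.05, power 0.8 and "two raters, and two measurements per participant". The result follows: "This calculation indicated a required sample size of 28–30 participants".
2. Criterion validity: an expected correlation of 0.75, alpha 0.05 and power 0.95, "yielding a minimum target sample size of 16 participants".
3. Loss: "Considering potential 10% data loss, 30 participants per group were planned".

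Section 4.1 fixes the size of the study: "Total of 60 participants". Section 3.2.3 randomises each participant to one of the two groups. Section 5.2 lists "10) Loss of data" among the exclusion criteria. The protocol gives no rule for replacing participants whose data are lost.

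**The concern.** The order of the text matters. The range 28–30 is presented as the output of the reliability calculation, and loss is brought in only afterwards, as a separate step covering both groups. Yet the planned group size equals the upper end of the range before any loss, so nothing has been added for the reliability group.

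Reliability is one of the study's stated purposes (section 2.1). A reader of section 4.2 would conclude that this group can lose a tenth of its data and still meet its requirement. On the plan's own figures it cannot. The validity group's surplus does not help, because participants are assigned to one group or the other.

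**Working it through.** **Inputs (section 4.2).** Required n is 28–30 for reliability and 16 for validity; loss is 10%; planned n is 30 per group.

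**Loss step.** Expected evaluable = planned × (1 − 0.10). Enrolment needed = required/(1 − 0.10), rounded up.

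| Group | Required | Enrolment needed | Planned | Expected evaluable | Against requirement |
|---|---|---|---|---|---|
| Reliability, lower end | 28 | 28/0.9 = 31.1 → 32 | 30 | 27 | 1 short |
| Reliability, upper end | 30 | 30/0.9 = 33.3 → 34 | 30 | 27 | 3 short |
| Validity | 16 | 16/0.9 = 17.8 → 18 | 30 | 27 | 11 over |

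The looser convention of multiplying by 1.1 gives 31 and 33 for reliability, still above 30. A planned 30 absorbs 10% loss only if the base requirement is 27 or less (27/0.9 = 30). If losses are independent at 10%, the chance of keeping at least 28 of 30 is 0.042 + 0.141 + 0.228 = 0.41.

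**Can the base figure be reproduced?** The usual approximation for testing an ICC of ρ1 against ρ0 with k ratings is

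n = 1 + 2(z_α + z_β)² k / [(k − 1)(ln C)²], with C = [1 + kρ0/(1 − ρ0)] / [1 + kρ1/(1 − ρ1)].

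The protocol does not state sidedness, so both are shown, with ρ0 = 0.6, ρ1 = 0.8 and power 0.80.

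- k = 2: C = 4/9, ln C = −0.811. One-sided, n = 1 + 2(2.486)²(2)/(0.811²) = 38.6 → 39. Two-sided, with 2.802 in place of 2.486, n = 48.7 → 49.
- k = 3: 27 one-sided, 33 two-sided.
- k = 4: C = 7/17, ln C = −0.887. One-sided, 22. Two-sided, n = 1 + 2(2.802)²(4)/(3 × 0.887²) = 27.6 → 28.

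Of these settings, only four ratings with a two-sided test gives a figure inside 28–30. By sections 3.2.1 and 3.5, each ICC uses two ratings: two sessions by one examiner, or two examiners scoring one session.

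**What the lost participants cost in power.** Power = P(F > c·C), where F has n − 1 and n(k − 1) degrees of freedom, c is its upper critical value (5% one-sided, 2.5% two-sided), and C is as above.

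| Setting | n = 30 | n = 28 | n = 27 | Cost of 30 → 27 |
|---|---|---|---|---|
| k = 2, one-sided | 0.70 | 0.67 | 0.66 | 0.04 |
| k = 2, two-sided | 0.58 | 0.55 | 0.54 | 0.05 |
| k = 4, two-sided | 0.84 | 0.82 | 0.81 | 0.04 |

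With k = 2, most of the distance from the stated 0.80 is already there at 30 with nobody lost.

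**The case against.** The strongest reply is that the gap is too small to matter. The requirement is a range, 27 is one below its lower end, and on the only setting tried that reproduces 28 (four ratings, two-sided) 27 still gives power of about 0.81, above the stated 0.80. This stands, and it is why the point is minor. It does not make the sentence correct: 27 is still below the figure the plan calls required.

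A second reply is that the sentence may mean only that the upper end of the range was chosen with loss in mind. Thirty against 28 allows two losses, or 6.7%, which is short of the 10% stated.

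A third is that listing lost data as an exclusion criterion could mean that such cases do not count towards the 60. The text does not exclude this, but it states neither replacement nor that 28–30 already includes loss. Either statement, if true, would settle the point.

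In the other direction, a reader might infer that the missing allowance brings power down from 0.80 to 0.66 or 0.54. The documents do not support that. Those values assume two ratings per ICC, and on that assumption power is already 0.70 or 0.58 at 30. The base figure accounts for most of the gap, and that is a separate matter from the loss allowance.

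**Conclusion.** Section 4.2 is wrong as written for the reliability group, and the error is minor. At the loss the plan itself expects, that group has about 27 evaluable participants, 1 to 3 below its stated requirement; an actual allowance would take 2 to 4 more enrolled. The validity group is fully covered.

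This rests on reading 28–30 as the requirement before loss, which is how the section presents it, and on no replacement of lost cases, since none is stated. It does not depend on any power figure, because the inconsistency holds even if 28–30 is accepted. The loss itself costs about 0.04–0.05 in power. Whether power at 27 is near 0.54, 0.66 or 0.81 depends on the number of ratings and the sidedness, so no single figure can be quoted until both are stated.

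**What to change.** Amend section 4.2, leaving enrolment at 30 per group:

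- Say that 30 per group are planned and that about 27 evaluable are expected in the reliability group after 10% loss.
- Limit the claim that loss is covered to the validity group (18 needed, 30 planned).
- Give power, or the expected confidence-interval precision of the ICC, at 27 evaluable, naming the number of ratings per ICC and whether the test is one- or two-sided. With two ratings, the power to report is about 0.66 one-sided or 0.54 two-sided.
- If 28–30 already includes loss, or if lost cases are replaced, say so instead.

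Raising the reliability group to 32–34 would repair only the loss step. With two ratings per ICC the base requirement is 39 one-sided or 49 two-sided, which inflates to 44 (39/0.9 = 43.3) or 55 (49/0.9 = 54.4), so that figure needs its own explanation.

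The cost is a few sentences and a less favourable stated figure. No procedure changes.

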##### **4.3. Study period**

The study is due to begin on 1 November 2024 and end on 31 May 2025.

#### **5. Eligibility criteria for research participants**

##### **5.1. Criteria for selection**

Participants will be recruited from patients who received occupational therapy at The Jikei University Medical Hospital during the study period. Participants will be those who meet all the following selection criteria and whose consent has been obtained.

- (1) Age 18 or older
- (2) Able to hold a sitting position independently
- (3) Has hemiplegia after stroke

##### **5.2. Exclusion Criteria**

- (1) impaired consciousness
- (2) Cognitive impairment (Mini-Mental State Examination score of 25 or below) or a diagnosis of post-stroke cognitive impairment affecting the ability to understand instructions or perform tasks
- (3) Recurrent stroke
- (4) Visual field impairment
- (5) Bilateral upper limb motor paralysis
- (6) CNS or orthopedic disease other than stroke
- (7) Upper limb or finger joint pain during movement
- (8) Significant limitation of joint range of motion of the upper limb
- (9) Amputation of upper limb, hand, or fingers
- (10) Loss of data

#### **6. Procedures for obtaining informed consent**

##### **6.1. Description of ethical considerations of the research**

#### 6.1.1. Regulatory Compliance

This research will be conducted in compliance with the "Declaration of Helsinki" and the "Ethical Guidelines for Life Sciences and Medical Research Involving Human Subjects (Ministry of Education, Culture, Sports, Science and Technology, Ministry of Health, Labor and Welfare, and Ministry of Economy, Trade and Industry, partially revised on March 10, 2022).

#### 6.1.2. Compliance with research protocol

All investigators participating in this study will comply with this research protocol as long as it does not compromise the safety and human rights of patients.

#### 6.1.3. Deviations from the research protocol

Researchers must not deviate from or change the research protocol before obtaining permission from the head of the research institution based on the Ethics Committee's prior review.

When the principal investigator becomes aware of a deviation or change, he/she shall promptly submit to the Ethics Committee the details and reasons of the deviation or change, and if a revision of the research protocol, etc. is necessary, a draft of the revision to the Ethics Committee and report it to the Ethics Committee and the head of the research institution. The principal investigator shall record all deviations from the research protocol together with the reasons for the deviation and the measures taken.

#### 6.2. How to give informed consent

This study is a study that falls under the following.

|    |                                                                                                                                                                                                                                                                                                                                          |
|----|------------------------------------------------------------------------------------------------------------------------------------------------------------------------------------------------------------------------------------------------------------------------------------------------------------------------------------------|
| 1. |  Invasive (including minor invasion)
 Non-invasive                                                                                                                                                                                                                         |
| 2. |  With intervention
 No intervention                                                                                                                                                                                                                                        |
| 3. |  (1) Use of newly acquired samples and information for research purposes
 (2) Use only newly acquired information for research purposes
 (3) Use existing samples and information
 (4) Use only existing information |
| 4. |  (1) There is transfer of samples and information to/from other institutions
 (2) No transfer of samples/information to/from other institutions                                                                                                                            |

This study utilizes information obtained within routine clinical practice; therefore, it will be conducted after obtaining written informed consent from research participants.

Researchers and others will provide the consent form approved by the ethics committee to the research participant (including a surrogate decision-maker when necessary; the same applies hereafter), provide sufficient explanation both verbally and in writing, and obtain written consent freely given by the research participant.

Researchers shall promptly provide information to research participants when information that could influence their consent is obtained, or when changes to the implementation plan or other aspects that could influence consent are made. They shall confirm the participants' intent regarding whether to participate in the research in advance.

Furthermore, they shall revise the consent explanation document and other materials after obtaining prior approval from the ethics committee and obtain renewed consent from the research participants.

## **7. Management of personal information**

### **7.1. Handling of Personal Information**

Researchers and heads of research institutions shall comply with the “Ethical Guidelines for Life Science and Medical Research Involving Human Subjects,” regulations and procedures established by the research institution, as well as the Personal Information Protection Act, ordinances, and other relevant laws and regulations regarding the handling of personal information, anonymized processed information, pseudonymized processed information, and personal-related information. Researchers shall appropriately handle personal information, etc., obtained while conducting research and held by the research institution to which the researcher belongs, to prevent leakage, loss, or damage and ensure other security management. The principal investigator shall, in cooperation with the head of the research institution, provide necessary guidance and management to other researchers, etc., handling such information to ensure the appropriate handling of held personal information, etc., during the conduct of research. When publishing the results of this research, researchers shall ensure that the information has been appropriately processed to prevent identification of specific individuals, thereby preventing any privacy-related disadvantage to research participants. Information that could identify specific individuals among the research participants involved in this research should not be shared with other research institutions or entities.

### **7.2. Method of processing in such a way that individuals cannot be identified**

Researchers shall process the samples and information collected in this study by removing personal information such as names, initials, and patient IDs, then assigning new research IDs or numbers (hereinafter referred to as “research IDs, etc.”) for handling purposes, thereby rendering the data unidentifiable to specific individuals.

When processing data to prevent identification of specific individuals, researchers will create a table or record (hereinafter referred to as a “correspondence table”) linking personal information to research IDs or numbers. This correspondence table will enable the restoration of pseudonymized information (pseudonymized data) back to its original personal information.

The correspondence table is used, when necessary, such as when a research participant withdraws consent or declines participation, to restore pseudonymized information to personal information and dispose of the relevant research participant's samples and information. The correspondence table is managed under the responsibility of the principal investigator and stored in a locked cabinet within the research institution.

Furthermore, when publishing the results of this research, information that could identify specific research participants must not be included.

## **8. Anticipated risks and benefits**

### **8.1. Expected profit**

Participation in this study will not directly benefit the research participants. However, it is anticipated that by verifying the reliability and validity of the new ARAT, this research will contribute to rehabilitation treatment planning and goal setting, enabling patients to receive effective treatment.

## 8.2. Anticipated burdens and disadvantages

The examinations and assessments conducted in this study are routine clinical procedures and are non-invasive; therefore, participation is not expected to cause any burden or disadvantage.

## 8.3. Anticipated Risks

All upper limb function assessments conducted in this study are performed within the scope of routine clinical practice, and no new risks arise from this research. Patients may experience physical and mental fatigue or feel unwell due to examinations and evaluations. These are matters also observed during routine clinical care.

## 8.4. How to minimize risk

The examiner will conduct the assessment while observing whether participants appear excessively tense and inquiring about their physical and mental fatigue levels. During evaluation, appropriate rest periods will be scheduled as needed, taking care to minimize physical and mental strain as much as possible. If continuing the study becomes difficult, it will stop immediately. Should any participant report feeling unwell, this will be reported to the rehabilitation physician for appropriate examination and treatment

### 8.4.1. Criteria for discontinuation of individual participants

Research on a case shall be discontinued if any of the following discontinuation criteria are met.

- (1) When a research participant voluntarily requests to withdraw their consent.
- (2) When the principal investigator or other researcher determines that continuing the research is difficult due to worsening of the primary disease or complications.
- (3) If a significant deviation from the research protocol is identified, such as a violation of ethical guidelines, inclusion criteria, or exclusion criteria.
- (4) If compliance with the research protocol becomes impossible.
- (5) If the entire study is discontinued.
- (6) In other cases where the principal investigator or other researchers determine that continuation of the study is difficult.

[Basis for setting up]

These measures were established to ensure ethical research conduct and to safeguard the safety of research participants.

[How to respond in the event of cancellation]

The principal investigator and other researchers shall take appropriate measures for participants when discontinuing a study due to meeting discontinuation criteria, and clearly document the date and timing of discontinuation, reasons, and circumstances in medical records or similar documentation. Furthermore, if consent is withdrawn after the initiation of study treatment, the cause—whether due to an adverse event or an incidental event—shall be clarified as much as possible.

### 8.4.2. Criteria for discontinuation of the entire study

The principal investigator shall, after careful consideration, decide to terminate or suspend the research as necessary if any of the following conditions apply:

- (1) When it is determined that patient recruitment is difficult and achieving the target number of participants is unlikely.

- (2) When the research objectives are achieved before reaching the target number of participants or the planned research period.
- (3) When the ethics committee recommends or orders termination.

## **9. Method of storage and disposal of samples and information**

### **9.1. Storage of Samples**

Since no samples are used in this study, this does not apply.

### **9.2. Storage of Information**

#### **9.2.1. Definition of information to be stored**

The information subject to retention in this study is defined as copies of various application forms and reports, notifications from ethics committees and heads of research institutions, correspondence records, consent documents, copies of case report forms, records pertaining to information provision, and other documents or records necessary to ensure the reliability of data, including medical records.

#### **9.2.2. Information storage method, storage period, and disposal method**

The principal investigator shall retain the source materials defined in Section 10.2.1 for a period of five years from the date this research concludes, or until three years have elapsed from the date the final publication of this research's results was reported, whichever is later. However, at research institutions that stipulate a longer retention period, the materials shall be retained for the period specified in the institution's internal regulations.

Storage shall be conducted in lockable storage facilities. Other matters should be appropriately stored according to each institution's procedures. Furthermore, information and data collected in this research shall be anonymized by removing personal information such as names, initials, and patient IDs, assigning new research IDs, etc., to ensure specific individuals cannot be identified. This anonymized information shall then be appropriately stored by the records custodian at each institution. Correspondence tables shall be strictly managed under the responsibility of each institution's research principal investigator, with measures implemented to prevent leakage or loss.

When disposing of materials after the retention period ends, data stored on computers shall be erased using data erasure software. Paper documents shall be shredded with care to protect personal information. If separate procedures exist at each institution, those procedures shall be followed for appropriate disposal.

### **9.3. Transfer of Samples and Information with Other Institutions**

This research does not involve the exchange of samples or information with other institutions and therefore does not apply.

## **10. Content and Method of Reporting to the Head of the Research Institution**

1) When the Principal Investigator intends to conduct research (including cases where the research plan is modified), they shall prepare a research plan, obtain approval from the Ethics Committee, and then receive implementation permission from the head of the research institution. Furthermore, the Principal Investigator shall notify the research leader at the collaborating institution of the Ethics Committee's approval outcome, and the research leader at the

collaborating institution shall receive implementation permission from the head of their affiliated medical institution.

2) If a principal investigator obtains facts or information that compromise the ethical validity or scientific rationality of the research, or information that may compromise them and is deemed likely to affect the continuation of the research, they shall report this without delay to the head of the research institution and the principal investigator. The principal investigator shall, as necessary, suspend or terminate the research, or modify the research plan.

3) If the Principal Investigator obtains facts or information that undermine the appropriateness of the research implementation or the reliability of the research results, or information that may potentially undermine them, they shall promptly report this to the head of the research institution and the Principal Investigator. The Principal Investigator shall, as necessary, suspend or terminate the research, or modify the research plan.

4) The Principal Investigator (or Research Manager) shall, in principle, report annually to the head of the research institution on the progress of the research and the status of storage and management of acquired information.

5) Upon completion (including discontinuation; the same applies hereinafter) of the research, the Principal Investigator shall report to the head of the research institution and to the Research Manager of the collaborating research institution. The Research Manager of the collaborating research institution shall report to the head of their affiliated research institution.

